### Experimental design

2.1

We will evaluate the implementation of *ecofit* using a hybrid type III implementation-effectiveness trial [37] involving 16 outdoor gym locations randomized to either the (i) ‘Low’ or (ii) ‘Moderate’ implementation support model. Assessments will be conducted at baseline, 3-months (primary and secondary outcomes) and 6-months (secondary outcomes only) and will commence in mid-2024. This implementation-effectiveness trial will be conducted across all outdoor gym locations (N = 16) in the Newcastle City (population n = 173,251) and Lake Macquarie (population n = 202,680) local government municipalities, New South Wales (NSW), Australia. The Standards for Reporting Implementation Studies (StaRI) initiative will be used in the reporting of this study [38]. Our study has received ethical approval from the University of Newcastle Ethics committee (H-2018-0060). The trial has been registered with the Australian and New Zealand Clinical Trial Registry (ANZCTR) (ACTRN12624000261516).

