### Recruitment, randomization and blinding

2.2

We have developed a promotional campaign to promote outdoor gym use across both local government municipalities; this will serve as the primary recruitment strategy for the study. The campaign will employ strategies, used in the *ecofit* effectiveness trial [31] and other, similar studies [39], including print and broadcast media, letter drops to all households within the same or adjacent suburbs of each outdoor gym, school/work newsletters, and social media, to promote the *ecofit* app and outdoor gym use. The promotional information will also emphasise the benefits of RT.

Randomization of the park location has already been conducted. Each outdoor gym was pair-matched based on the socioeconomic status of the area surrounding the facilities (high versus low). This classification was estimated using an established socioeconomic status consensus-based index (i.e., the SEIFA index of relative socio-economic advantage and disadvantage) [40]. Parks within each pair were randomized to one of the two conditions (i.e*.,* ‘Low’ or ‘Moderate’ implementation support). The randomization procedure was conducted by a researcher not part of the core research team. The randomization outcome for each location can be found in supplementary material 1. Data collection will be blinded to group allocation.

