##### Reach

2.7.1.1

The primary outcome ‘reach’ is defined as the difference in the absolute number (3-month minus baseline assessments) of outdoor gym users (i.e., people using the outdoor gyms for RT activities) between the two implementation models. This will be measured using a ‘modified version’ of the *System for Observing Play and Recreation in Communities* (SOPARC Resistance Training (hereafter referred to as SOPARC-RT)) [41].

SOPARC-RT has been specifically adapted to capture additional data (not included in the original SOPARC protocol [48]) by coding the interaction with the outdoor gym equipment (i.e., ‘using equipment for RT,’ ‘completing RT without equipment,’ ‘stretching using equipment’ and ‘using equipment for aerobic exercise’) [41]. Each park will have one predetermined target area (i.e., either a pod or one station along a trail) which has been identified for observations during the outdoor gym audit. If the outdoor gym location is classified as a pod/trail, the pod will be selected for observation. At all target areas, one trained research assistant will conduct the observations from a position where the outdoor gym equipment is clearly visible. SOPARC-RT will employ similar recording procedures for ‘jogging tracks’ as per the original SOPARC protocol [48] for all parks regardless of outdoor gym type, and each observation period (shift) will result in 2 h-long observations, as opposed to systematic scans as used in SOPARC. The research assistant observing the target area will code each individual by gender (i.e., woman, man, unsure), and perceived age category (i.e., adult [18–59 years], or senior [60 years or older]). The SOPARC-RT observation tool is attached in supplementary material 3.

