The observation schedule will cover two days per park (i.e., one weekday and one weekend day). Each day will be divided into three observation shifts: morning (0600–0800 on weekdays, 0630–0830 on weekends), midday (1200–1400), and evening (1600–1800) [41,48]. Cancelled shifts due to inclement weather (e.g., actual or threat of heavy rain and/or thunderstorm) will be replaced on the following day or on the same day of the subsequent week if weather remains inclement [41,48]. Baseline and follow-up (3-months) observations will be conducted by a team of research assistants over a four-week period at baseline, and 3-months. Pair-matched parks will be observed on the same days. Conducting observations on different days and times over a set period of time is a typical approach for outdoor park observational studies monitoring physical activity [49]. Each park will be assessed over two days with three observation periods per day, totalling six observation periods at baseline and six observation periods at follow-up (3-months). The total number of people observed across these six observation periods will be summed separately for the baseline and follow-up assessments.

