### Statistical analysis

2.9

Statistical analyses of the primary (i.e., reach) and secondary (except for fidelity) outcomes will be conducted with generalised linear models adjusted for the baseline value of the outcome using IBM SPSS Statistics version 30 (IBM Corporation, Armonk, NY) for Windows computers. These models will include fixed effect for study group, baseline value of the outcome, and stratification variables (i.e., high versus low SEIFA value). We will explore descriptive statistics and conduct a moderator analysis on the moderate implementation support strategies (i.e. face to face sessions, QR codes at park) to determine their independent impact on our primary outcome of park use. Additional exploratory sub-group analyses of the intervention effect on the primary (i.e., reach) and secondary outcomes (i.e., uptake, dose received, usage and impact) will be conducted using generalised linear models adjusted for the baseline value of the outcome (i.e., group-by-moderator) by gender (i.e., woman, man, unsure) and age (i.e., adults [18–59 years], and seniors [60 years or older]). Descriptive statistics will be used to examine the other secondary outcome of the study (i.e., fidelity) and the implementation determinants (i.e., acceptability, feasibility, dose satisfaction and cost). Sensitivity analyses will examine the robustness of the findings considering the quality of the outdoor gym facilities (based on the audit tool). Analysis of app usage data will include descriptive statistics and Cox Regression to examine time to non-usage attrition as in prior studies [51,52].

To detect a Cohen's d of 1 (strong effect), we estimate that ∼2 individuals will be observed using the outdoor gyms as intended per day per park (17 individuals in total in each group per day) assuming 80 % power and p = 0.05. Taking clustering by park into consideration and assuming an ICC of 0.05, then the design effect is 1.05, resulting in ∼3 individuals per day/park (24 individuals in total in each intervention group, total n = 48). From our previous work, this number is reasonable to expect [39,41].

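### The primary model for reach rests on 16 park totals but is not tied to an absolute scale or small-sample inference; usual large-sample GLM tests would exceed the nominal 5%

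*Protocol article*

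**What the plan says.** All references are to the protocol article.

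- **Model (2.9 Statistical analysis).** The primary and most secondary analyses "will be conducted with generalised linear models adjusted for the baseline value of the outcome using IBM SPSS Statistics version 30". The terms are given as "These models will include fixed effect for study group, baseline value of the outcome, and stratification variables (i.e., high versus low SEIFA value"). Distribution, link, scale estimator and reference distribution are not named.
- **Units (2.1 Experimental design).** The trial has "16 outdoor gym locations randomized to either the (i) ‘Low’ or (ii) ‘Moderate’ implementation support model".
- **Allocation (2.2 Recruitment, randomization and blinding).** Parks were matched on high or low SEIFA, and "Parks within each pair were randomized to one of the two conditions".
- **Outcome (2.7.1.1 Reach).** Reach is "defined as the difference in the absolute number (3-month minus baseline assessments) of outdoor gym users", compared between the two support models.
- **Data (2.7.1.1 Reach).** On observation days: "The observation schedule will cover two days per park (i.e., one weekday and one weekend day"). On the counts: "The total number of people observed across these six observation periods will be summed separately for the baseline and follow-up assessments". I read this as one total per park at each assessment.

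**The concern.** Two things are left open that matter with so few units.

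**Calibration.** The standard tests that accompany a generalised linear model (Wald chi-square, likelihood ratio) are large-sample approximations. With 16 values and 4 fitted parameters they are not close to their nominal level. A Poisson model with scale fixed at 1 also assumes that park totals vary no more than chance counts do. The protocol's own description makes that doubtful: section 2.5.3 reports between three and 19 pieces of equipment per gym and three gym types, and section 2.9 assumes a non-zero ICC between users of the same park.

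**Scale.** Reach is a difference in absolute change. A log-link model of the 3-month count would estimate a ratio, and a Poisson or negative binomial model could not take the change itself as response, since a change can be negative.

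The trial has one primary test, and its result is meant to advise councils on whether the added support is worth providing. If that test is liberal, Moderate support could be declared better well above 5% of the time when it makes no difference.

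**Working it through.** **1. The plan's own figures.** The only error rate stated is p = 0.05. The sample-size figures reproduce and supply the expected counts:
- Two-sample t-test, d = 1, two-sided 0.05, 80% power: 16.7, so 17 per group.
- Design effect 1 + (2 − 1) × 0.05 = 1.05.
- 17 × 1.05 = 17.85 per group; 17.85 / 8 = 2.23 per park; rounded up to 3; 3 × 8 = 24 per group.
- Over two observation days, 2 to 3 users per day is 4 to 6 users per park per assessment.

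**2. Degrees of freedom.** n = 16 parks; parameters are intercept, group, baseline and SEIFA stratum, so p = 4 and n − p = 12.

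**3. Normal model, exact type I error.** Under normality the group statistic has a t distribution on 12 df. Each large-sample test is the t test with a different cut-off:

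| Test at nominal 5% | Rejects when \|t\| exceeds | True level |
|---|---|---|
| t or F on 12 df | 2.179 | 5.0% |
| Pearson scale, Wald chi-square | 1.960 | 7.4% |
| Likelihood ratio | √[12 × (e^(3.841/16) − 1)] = √3.256 = 1.805 | 9.6% |
| ML scale, Wald chi-square | 1.960 × √(12/16) = 1.697 | 11.5% |

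These need no assumption about dispersion.

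**4. Count models, by simulation under no effect.** The protocol gives no dispersion, so it is assumed here: 16 parks in 8 pairs, gamma-Poisson counts, mean 4 or 6 per park per assessment, between-park CV 0.5 or 1.0, park-by-time CV 0 to 0.5. There were 600 runs per setting, baseline entered raw or logged, and no SEIFA or pair effect was simulated. Simulation error is about 1 to 2 percentage points per setting.

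| Analysis | Type I error across settings |
|---|---|
| Poisson, scale fixed at 1, Wald | 10.7% to 42.5% |
| Poisson, sandwich variance, Wald | 10.5% to 20.2% |
| Negative binomial, estimated dispersion | 5.9% to 16.9% |
| Normal, ML scale, Wald chi-square | 8.7% to 14.5% |
| Poisson, Pearson scale, t on 12 df | 4.0% to 11.3% |
| Normal, t on 12 df | 3.2% to 6.2% |
| Negative binomial, dispersion fixed at 1 | 0% to 5.5% |

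A separate set of 18 scenarios (2,000 trials each) gave 8% to 40% for fixed-scale Poisson with extra variation, and about 4% with none. It gave 3.5% to 5.0% both for the linear model with t on 12 df and for re-randomisation within pairs.

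A large-sample approximation shows what drives the Poisson figure. With over-dispersion factor φ, the level is about 2 × Φ(−1.96/√φ): 5% at φ = 1, 9.8% at 1.4, 16.6% at 2, 25.8% at 3 and 38.1% at 5.

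**5. Scale.** In a normal identity-link model with baseline as covariate, the response can be the 3-month count Y₃ or the change Y₃ − Y₀. Subtracting Y₀ from the response lowers the baseline coefficient by exactly 1 and leaves the group coefficient unchanged. That coefficient is a difference in absolute users, as section 2.7.1.1 requires. With a log link, the exponentiated group coefficient is a ratio of expected counts.

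**The case against.** The strongest case against is that nothing harmful has been fixed. The article names no distribution, link or test. A normal identity-link model is itself a generalised linear model, the three terms proposed below are already the protocol's, and such details are commonly left to an analysis plan.

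Much of this stands, and it rules out three stronger readings that a reader might draw:

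- **That the model contradicts the definition of reach.** It does not. An identity link returns the absolute difference defined in section 2.7.1.1. A mismatch arises only with a log link, which the text neither states nor excludes.
- **That the trial's false-positive rate is 10% to 40%.** The documents do not support this as a fact. The range belongs to a Poisson model with scale fixed at 1 and to over-dispersion that the protocol does not give. Other permitted choices hold 5% or lie below it.
- **That leaving the pairs out of the model inflates the error rate.** This is not shown. SEIFA level, the matching factor, is in the model, and the linear model without pair terms performs as well as re-randomisation within pairs.

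Missing family or link would not be a point by itself. What remains is that the protocol chose a model class, a set of terms and a unit count for which the usual large-sample inference is liberal. For the normal model that follows by exact calculation, without assumptions about the data beyond normality.

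**Conclusion.** The point holds in conditional form and should be addressed. With 16 park totals and 12 residual degrees of freedom, large-sample tests of a normal model have true levels of 7.4% to 11.5% instead of 5%. Fixed-scale Poisson inference reaches roughly 10% to 40% at 4 to 6 users per park under the assumed over-dispersion, and about 4% if there is none. A normal model with a t or F test stays close to 5%, and a negative binomial model with dispersion fixed at 1 does not inflate. The conclusion assumes that each park contributes one total per assessment. The count-model figures also depend on the assumed variation between parks and over time. The documents show that a liberal test is allowed, not that one has been chosen.

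**What to change.** State in section 2.9 that the primary analysis is a park-level linear model (normal, identity link) of the change in users from baseline to 3 months, or equivalently of the 3-month count. The terms are group, baseline count and SEIFA stratum, and the group effect is tested with a t reference on 12 residual degrees of freedom. The group coefficient is then the absolute difference that defines reach.

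If a log-link count model is also reported, label it a secondary ratio estimate, with estimated dispersion and a t reference. Even so, its level reached about 11% in one simulated setting, so it should not replace the linear model.

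A re-randomisation test within the 8 pairs is an optional sensitivity analysis. In power runs it lost up to about 9 percentage points against the linear model, so it is not proposed as the primary test.

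The cost is one or two sentences, with the same data and software. The downside is that the calibrated test rejects less often: the cut-off for |t| is 2.179, against 1.697 for the ML-scale Wald test.

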**Research design and methods:**

This hybrid type III implementation-effectiveness study will be evaluated using a two-arm randomized controlled trial, including 16 outdoor gym locations in two large regional municipalities in New South Wales, Australia. Outdoor gym locations will be pair-matched, based on an established socio-economic status consensus-based index (high versus low), and randomized to the ‘Low’ (i.e., *ecofit* app only) or ‘Moderate’ (i.e., *ecofit* app, face-to-face workout sessions and QR codes) implementation support group. The primary outcome of ‘reach’ will be measured using a modified version of the ‘System for Observing Play and Recreation in Communities’, capturing outdoor gym use amongst community members.

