### Intervention components, delivery, and implementation strategies

2.4

This study will assess the implementation-effectiveness of two different implementation support models promoting the ecofit intervention, which are outlined in Fig. 2 (i) Low support (i.e., *ecofit* app): versus (ii) Moderate support (i.e., *ecofit* app, face-to-face workout sessions and QR codes). These implementation support strategies were guided by the findings from our previous studies [30,31,41,42]. See Table 1 for an overview of the two main previous studies.

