#### Face-to-face training sessions

2.6.1

Three, 1-h face-to-face, on-site, group-based exercise sessions, led by a trained fitness professional, will be implemented as part of the Moderate implementation support model. The sessions will be conducted within the first month of the intervention, on set times and days (i.e., weekdays and weekends), and individuals can register to attend the sessions free of charge. Each session will encompass a complete standardised resistance and aerobic-based workout, which has been tailored to the outdoor gym location (i.e., workouts will vary pending availability of equipment). Workouts will follow the same structure as in the *ecofit* app (i.e., 3 x upper body, 3 x lower body and 2 x core exercises, and each exercise will be completed as 2 sets of 10 repetitions) [45]. The aerobic component will vary depending on outdoor gym type (i.e., trail, pod, or trail/pod). For outdoor gym pods, the aerobic activity may include short bursts of aerobic activities between each resistance activity (e.g., star jumps, 100-m walk/run out of/back to the pod, marching/running on the spot) or a longer walk/run after completing the resistance-based exercises. The trail locations will provide the opportunity for aerobic activity when moving between equipment. In addition to the workout, the group-based sessions provide an opportunity to ask questions about the *ecofit* app and receive feedback on their exercise technique. To advertise the face-to-face training sessions, posters will be placed on or near the outdoor gym equipment where the workout sessions will be held, along with schools, shopping centres and community notice boards in suburbs surrounding the outdoor gym locations. Exercise sessions will also be advertised via email to those app users who indicate living within the same postcode of the outdoor gyms allocated to Moderate implementation support model, during the app registration.

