## Discussion

3

This protocol describes the *ecofit* implementation-effectiveness trial, which has been adapted from the *ecofit* efficacy and effectiveness trials [29,30]. *Ecofit* is a multi-component community-based intervention aimed at increasing participation in resistance and aerobic-based physical activity using smartphone technology, the outdoor built environment, and social support. The objective of our current trial is to test a ‘Low’ versus a ‘Moderate’ implementation support model of the *ecofit* intervention in two large regional municipalities in New South Wales, Australia, on the reach (primary outcome), uptake, dose received, impact and fidelity. The main innovation of this study is to test whether an mHealth intervention with additional implementation strategies can increase outdoor gym use in the community [41].

*ecofit* represents a novel and scalable approach for the promotion of RT using outdoor gyms and mHealth. RT interventions targeting the general population are scarce, as most studies to date have predominantly focused on clinical populations using supervised modes of delivery [[53], [54], [55], [56], [57], [58], [59]]. Outdoor gyms provide an opportune delivery setting, as facilities are being rapidly installed around the globe (including Australia), offering free and accessible workout apparatus to perform physical activities (particularly RT) [60]. Despite the large number of installations, the facilities are generally poorly used, and few interventions have been trialled to increase usage [41,60]. The *ecofit* app provides a potentially cost-effective tool for local government agencies to promote the use of the facilities. If the additional support strategies (i.e., app only or inclusion of face-to-face introductory sessions and QR codes promoting app downloads) are deemed effective, they will provide councils with additional approaches to increase outdoor gym use. We plan to share our study findings with our local council partners and other local government agencies.

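### The planned moderator analysis cannot separate the effects of face-to-face sessions and QR codes, because every Moderate park gets both and no Low park gets either

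*Protocol article*

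**What the plan says.** The design has two arms. Section 2.1 describes a trial "involving 16 outdoor gym locations randomized to either the (i) ‘Low’ or (ii) ‘Moderate’ implementation support model", and Section 2.2 says "Parks within each pair were randomized to one of the two conditions". The Low model is the *ecofit* app alone. The Moderate model adds to the app, in the words of Section 2.4, "face-to-face workout sessions and QR codes".

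The component descriptions agree with this. Section 2.6.1 says the sessions "will be implemented as part of the Moderate implementation support model", and Section 2.6.2 places the QR codes at the Moderate locations. The last column of Table 1 assigns both to the intervention parks. Nowhere does the article describe a Moderate park with only one strategy, a Low park with either, or staggered introduction of the two.

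Section 2.9 then promises to "conduct a moderator analysis on the moderate implementation support strategies (i.e. face to face sessions, QR codes at park) to determine their independent impact", with park use as the outcome. The same sentence also mentions descriptive statistics.

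The Discussion refers to what follows "If the additional support strategies (i.e., app only or inclusion of face-to-face introductory sessions and QR codes promoting app downloads) are deemed effective".

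**The concern.** An independent impact of two strategies can be estimated only if one varies while the other is held fixed. Here the allocation ties them together and ties both to study group. A moderator of the group effect must also vary within at least one arm, and the provision of neither strategy does.

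What is at stake is how a supplementary result on the primary outcome would be read. Trainer-led sessions and QR signs are different kinds of support. A coefficient presented as the separate effect of one of them would be produced by software conventions for aliased terms, or by a non-randomised comparison of a few parks, and not by the trial's randomisation.

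**Working it through.** The plan gives no figure for this analysis. Its sample-size calculation covers only the two-group comparison. The 17 per group reproduces (two-sided t-test, d = 1, 80% power, alpha 0.05: 16.7, rounded up), but the point does not depend on it.

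**Inputs**
- Parks: 16, two conditions, randomised within pairs (Sections 2.1, 2.2). If each of the 8 pairs is split, there are 8 parks per arm. This agrees with Section 2.9, where 24 individuals per group at 3 per park gives 24 / 3 = 8 parks.
- Outcome: one summed count per park at each assessment (Section 2.7.1.1).
- Model terms: study group, baseline value, SEIFA stratum (Section 2.9).
- Provision: sessions (F) and QR codes (Q) at Moderate parks only, both at all of them (Abstract; Sections 2.4, 2.6.1, 2.6.2; Table 1).

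**Step 1: provision indicators.** Let G = 1 for Moderate and 0 for Low. By design F = Q = G for every park. The linear predictor

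b0 + b1·baseline + b2·SEIFA + bF·F + bQ·Q

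therefore equals

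b0 + b1·baseline + b2·SEIFA + (bF + bQ)·G.

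Replacing (bF, bQ) by (bF + t, bQ − t) leaves the fit unchanged for any t. The data inform only the sum.

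**Step 2: rank check for 16 parks allocated 8:8.** Placeholder baseline counts were used; the result does not depend on their values.

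| Columns | Number | Rank |
|---|---|---|
| Intercept, baseline, SEIFA, F, Q | 5 | 4 |
| The same plus G | 6 | 4 |
| Intercept, baseline, SEIFA, G, F, G×F | 6 | 4 |
| For comparison: F and Q varied in a 2×2 layout | 5 | 5 |

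In the first row, bF alone is not estimable, bQ alone is not estimable, and bF + bQ is. Adding group or a group-by-component product adds no information. Only the 2×2 layout, which this trial does not use, identifies both effects. More parks under the same allocation would not help, because the problem is identification and not power.

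**Step 3: exposure instead of provision.** Section 2.7.2.2 counts session attendance, which can differ between Moderate parks. An attendance term would therefore not be collinear with group. But attendance arises after randomisation and does not exist in Low parks, so its coefficient would come from comparing about 8 Moderate parks with each other. Within those parks, a model with intercept, baseline, SEIFA and attendance leaves 8 − 4 = 4 residual degrees of freedom, and a busier or better-liked park could have both higher attendance and higher observed use. For QR codes there is no equivalent: Section 2.7 does not list scans as an outcome.

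**The case against.** The best defence is that Section 2.9 does not define the moderator variable. That detail can properly be left to an analysis plan that is not shown, and the investigators may intend attendance and not provision. This stands in part. A reader might infer that any component analysis must fail through collinearity. The documents do not support that, because an attendance term could be fitted. But such a term gives a non-randomised association and not an independent impact, and it offers nothing for QR codes. No analysis plan can supply variation that the allocation lacks. The park-by-park allocation in Supplementary material 1 is also not shown, but nothing in the article suggests that components differ between Moderate parks.

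The second defence concerns scope, and it stands. The clause describes a supplementary analysis, and the sentence after it introduces additional exploratory subgroup analyses, which suggests that this one is exploratory too. A reader might infer that the primary result is compromised. It is not: the primary model compares Moderate with Low, which is the stated objective and the definition of reach.

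A reader might also infer that councils will be told which component to fund. The article does not say so. The Discussion passage on council use names sessions and QR codes together as one option.

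Finally, the Discussion phrase that includes app only might be taken as a planned claim that the app works against no app, or as a planned Low-arm before-after analysis. Section 2.9 contains neither, and the phrase can be read as loosely naming the two models.

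**Conclusion.** The stated aim cannot be met. As provided, sessions and QR codes are completely confounded with each other and with study group: of the two separate component effects, none is estimable, and only the combined package effect is. An exposure-based version would be an observational association among about 8 parks for attendance, with no listed measure for QR codes.

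This rests on two assumptions: that both strategies go to all Moderate parks and to no Low park, as every relevant section says, and that each pair is split, giving 8 parks per arm. The rank result does not need the exact 8:8 split.

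The point should be fixed, but it is not critical. The sample size, the allocation and the primary Moderate-versus-Low analysis are untouched. The Discussion's mention of app only is a minor wording matter: both arms receive the app, so the randomised comparison cannot show that the app alone is effective.

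**What to change.** 1. In Section 2.9, delete the aim of determining independent impact and the moderator analysis of the two components.
2. State there that the randomised comparison estimates the effect of the Moderate package (sessions plus QR codes, added to the app) versus app only, and that the contributions of its parts cannot be separated.
3. Keep the descriptive statistics already planned. Report session attendance for each Moderate park, and QR scans if they happen to be recorded, as process measures with no component-level causal claim. If attendance is related to park use at all, label the result as non-randomised and exploratory.
4. In the Discussion, reword the phrase so that it refers to the added support and does not imply that app only can be deemed effective.

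The cost is a few sentences. No new data collection is required; park-specific QR links would be an optional extra. Varying the two strategies separately would identify their effects, but Section 2.2 says randomisation has already been done, so correcting the wording is the realistic course.

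### The power statement counts observed gym users as the sample size, but reach is one count per park with 8 parks per arm, so the stated 80% power for d = 1 is unsupported

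*Protocol article*

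**What the plan says.** The power paragraph in section 2.9 (Statistical analysis) opens "To detect a Cohen's d of 1 (strong effect), we estimate that" about 2 "individuals will be observed using the outdoor gyms as intended per day per park (17 individuals in total in each group per day"), with the error rates given as "assuming 80 % power and p = 0.05". It then continues: "Taking clustering by park into consideration and assuming an ICC of 0.05, then the design effect is 1.05, resulting in" about 3 people per park per day, or "24 individuals in total in each intervention group", with a total of 48.

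The design and the outcome are described elsewhere in the same article:

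- Section 2.1 (Experimental design) describes a trial "involving 16 outdoor gym locations randomized to either" Low or Moderate support. Section 2.2 says that the parks were matched in pairs and randomised within pairs, which gives 8 per arm.
- Section 2.7.1.1 (Reach) defines the primary outcome as the change from baseline to 3 months in the number of people using the gym for resistance training, compared between the two models. Each park has six observation periods per assessment, and "The total number of people observed across these six observation periods will be summed separately for the baseline and follow-up assessments".
- Section 2.9 names a generalised linear model with terms for group, the outcome's baseline value and SEIFA stratum.

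**The concern.** In a calculation for a difference in means, n counts the units that each contribute one outcome value. For reach, a passer-by contributes no outcome value; he or she adds one to the park's count. Seeing more people raises the outcome and does not add units. The planned model confirms this, because a baseline value of reach exists for a park and not for an anonymous visitor. An ICC and design effect for people nested in parks therefore do not apply to this endpoint.

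Reach is the only primary outcome, and the findings are meant to inform councils' decisions about promoting gym use. If true power is well below 80%, a real effect of the planned size could easily be missed. A reader relying on the stated figure would then give a non-significant result more weight than the design can bear. Section 3 (Discussion) itself expects scaled-up programmes to show smaller effects than the trials before them, so d = 1 is already a demanding target.

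**Working it through.** **Inputs from the protocol article.** d = 1, 80% power, p = 0.05, 17 then 24 people per group, ICC 0.05, design effect 1.05 (all section 2.9); 16 parks randomised within pairs, so 8 per arm (sections 2.1 and 2.2); one summed count per park per assessment (section 2.7.1.1). The SD behind d, the sidedness of the test and the correlation between baseline and follow-up are not stated.

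**Formula.** For a two-sample t-test with n per arm, the noncentrality is d × sqrt(n/2). Power is the probability that a noncentral t variable exceeds the critical value in either direction.

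**1. Reproducing the plan's figures.**
- n = 17, d = 1, two-sided 0.05: power 80.7%. With n = 16 it is 78.1%. So 17 is the exact two-sided answer. One-sided testing needs about 13 (normal approximation) and does not match.
- Design effect at 2 people per park: 1 + (2 − 1) × 0.05 = 1.05.
- 17 × 1.05 = 17.85 per group; 17.85 / 8 = 2.23 per park, rounded up to 3; 3 × 8 = 24 per group, 48 in total.

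The stated figures are thus a person-level t-test, inflated and then rounded up to whole people per park.

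**2. The same d with the park as the unit.**
- n = 8 per arm, d = 1: noncentrality = 1 × sqrt(8/2) = 2.0.
- 14 df (no covariates): power 46.1%.
- 12 df (16 parks less intercept, group, baseline and SEIFA): power 45.2%.
- d detectable with 80% power: 1.51 (14 df) or 1.53 (12 df).
- One-sided 0.05 would give 60%, still short of 80%.

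**3. Crediting baseline adjustment.** Suppose that d = 1 is on the raw SD and that adjustment for a baseline correlated r with follow-up shrinks the residual SD by sqrt(1 − r²). The effective d is 1 / sqrt(1 − r²), with 12 df. The values of r are assumptions.

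| r | effective d | power |
|---|---|---|
| 0.3 | 1.05 | 49% |
| 0.5 | 1.15 | 56% |
| 0.7 | 1.40 | 73% |
| 0.8 | 1.67 | 86% |

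Power of 80% needs an effective d of 1.526, that is r = sqrt(1 − 1/1.526²) ≈ 0.76.

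**4. Count scale, illustrative only.** Assume 6 people per park per assessment (3 per day × 2 days) and a residual between-park coefficient of variation CV. The detectable rate ratio is exp[(t(0.975, 12 df) + t(0.80, 12 df)) × sqrt(2 × (1/6 + CV²)/8)]. This gives 1.9 at CV = 0, 2.2 at CV = 0.3 and 2.7 at CV = 0.5. Neither the 6 nor the CVs come from the protocol as park-level assumptions, and reach is defined as a difference, not a ratio.

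**The case against.** Four points deserve a hearing.

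- **The design-effect step.** A reader might infer that it is an arithmetic error, since 24/17 = 1.41 and not 1.05. The documents do not support that: the rest of the increase is rounding 2.23 up to 3 people per park. There is a small mismatch, because 1.05 belongs to 2 people per park and the final 3 would give 1 + 2 × 0.05 = 1.10. It changes nothing: 17 × 1.10 = 18.7, or 2.34 per park, which still rounds up to 3 and gives 24.
- **The 46%.** A reader might take this as the trial's actual power. It is conditional on d = 1 being measured on the SD of the park-level outcome as analysed, which the protocol does not say. The planned model adjusts for baseline, and with a correlation of about 0.76 or more 80% would be reached. No document rules that correlation in or out. This objection stands, and it is why the result must be given as a range.
- **A person-level reading.** If each visitor had a measured outcome with ICC 0.05, the mean of 3 people per park would have a standardised difference of 1 / sqrt(1.10/3) = 1.65, and 8 parks per arm would give 87% power. That would defend the calculation for some other endpoint. No person-level value of reach is defined, so it does not help here.
- **Consequences.** A reader might infer that too few parks were chosen, or that the authors intend to read a null result as no effect. Section 2.1 includes every outdoor gym location in both municipalities, so the calculation did not set the number of parks. Nothing in the article says how a null result will be read. The risk of over-reading is a reason for care in wording, not something that the plan commits to.

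**Conclusion.** The point holds as an error in the unit of analysis, not in the arithmetic. The stated 80% power for d = 1 belongs to a comparison of 17 or more independent people per group, whereas the trial compares 8 park counts per arm. On the park-level SD, power for d = 1 is about 46% (45% with the planned covariates' degrees of freedom), and the detectable d is about 1.5. If d is on the raw SD, power could lie anywhere from about 49% to 86% over assumed correlations of 0.3 to 0.8.

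These figures assume a two-sided 5% test and approximately normal park-level values; the article does not name the distribution for the generalised linear model. They show that the 80% is unsupported. They do not show that it is unattainable.

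**What to change.** In section 2.9, delete the person-based calculation, including the individual-level ICC, the design effect and the total of 48. Replace it with a statement of power or detectable effect for 16 parks, 8 per arm, with the park as the unit. Give the assumed SD of the park-level outcome and the assumed correlation between baseline and 3-month counts, with their source, and say which SD any standardised effect refers to. If the correlation is uncertain, show the result over a range, as in the table above.

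Add a sentence saying that the primary result will be interpreted through its estimate and confidence interval, and that a non-significant difference will not be read as no effect. A detectable rate ratio is optional.

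The cost is a change of wording and, in all likelihood, a less favourable stated power. No parks, observations or changes to the planned model are needed.
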